## Abstract

**Background:**

Up-to-date and accurate information about the health problems encountered by primary care doctors is essential to understanding the morbidity pattern of the community to better inform health care policy and practice. Morbidity surveys of doctors allow documentation of actual consultations, reflecting the patient’s reason for seeking care as well as the doctor’s diagnostic interpretation of the illness and management approach. Such surveys are particularly critical in the absence of a centralized primary care electronic medical record database.

**Objective:**

With the changing sociodemographic profile of the population and implementation of health care initiatives in the past 10 years, the aim of this study is to determine the morbidity and management patterns in Hong Kong primary care during a pandemic and compare the results with the last survey conducted in 2007-2008.

**Methods:**

This will be a prospective, practice-based survey of Hong Kong primary care doctors. Participants will be recruited by convenience and targeted sampling from both public and private sectors. Participating doctors will record the health problems and corresponding management activities for consecutive patient encounters during one designated week in each season of the year. Coding of health problems will follow the International Classification of Primary Care, Second Edition. Descriptive statistics will be used to calculate the prevalence of health problems and diseases as well as the rates of management activities (referral, investigation, prescription, preventive care). Nonlinear mixed effects models will assess the differences between the private and public sectors as well as factors associated with morbidity and management patterns in primary care.

**Results:**

The data collection will last from March 1, 2021, to August 31, 2022. As of April 2022, 176 doctor-weeks of data have been collected.

**Conclusions:**

The results will provide information about the health of the community and inform the planning and allocation of health care resources.

**Trial Registration:**

ClinicalTrials.gov NCT04736992; https://clinicaltrials.gov/ct2/show/NCT04736992

**International Registered Report Identifier (IRRID):**

DERR1-10.2196/37334

## Introduction

Primary care is the setting where the majority of people will seek health care. Studies on the ecology of health care show this is the case in the United States, where 52% of patients who consulted a doctor in the past month saw a primary care doctor [1], and also in Hong Kong (84.5% of patients) [2]. Information about the health problems of patients presenting in primary care is therefore crucial to understanding the health of the general community for the planning and allocation of health care resources.

It is important to replicate morbidity surveys from time to time given changing demographic and socioeconomic profiles. In Hong Kong, the last morbidity study was carried out in 2007-2008 [3]. Within the last 10 years (2005-2015), there has been an increase in the proportion of people aged 65 years or older, level of educational attainment, individual and household income, and cross-border immigration from mainland China, while there has been a notable decline in unemployment [4]. These sociodemographic changes are reflected in the health problems and concerns of patients who present to primary care and also in the changing prevalence of various diseases over time [5,6]. Practice-based morbidity surveys conducted at 10-year intervals have been able to capture changes in the prevalence and trends of health problems presenting in primary care as observed in England and Wales (1991-2001) [6] and in Hong Kong (1994-2007) [3,7].

Superimposed on this background is the expectation that chronic disease and psychological problems will continue to be a major burden of illness globally and in Hong Kong as we move deeper into the 21st century [8]. There is increasing pressure for primary care to shoulder the care for the majority of these patients given the volume of patients and the demonstrated effectiveness and cost-effectiveness of family doctor–led primary care [9]. Local Hong Kong evidence shows that chronic disease makes up an increasing proportion of problems seen by primary care doctors, with the bulk of patients seen in public outpatient clinics [10].

Since the last morbidity study in Hong Kong in 2007-2008 [3], the Hong Kong Government has implemented some primary care initiatives in response to the increasing burden on public general outpatient clinics (GOPC) such as the GOPC Public-Private Partnership, Elderly Health Care Voucher Scheme, and the Vaccination Subsidy Scheme. These aim to encourage patients to seek care in the private sector, particularly for care of chronic diseases. Tracking morbidity and management trends would provide an indication of the impact of these initiatives on the prevalence of chronic disease and its care in both public and private primary care sectors.

Apart from the morbidity pattern, specific information on the management pattern such as prescription, investigation, referral to specialists, health promotion, and disease prevention is important for assuring the quality of primary care services and for identifying support services needed. In 2014-2015, there were an estimated 6 million primary care encounters in the public sector alone [11], which extrapolates to about 30 million primary care encounters in the combined public (20% of total encounters) and private sectors across Hong Kong [12]. The most recent morbidity study found that the Hong Kong referral rate to specialists was 2.5% in 2007-2008 [3], which means that even a small increase of 1% in referral rate would produce a huge relative increase of 40%, translating to an additional 300,000 specialist referrals. Changes in consultation trends in primary care do occur [13], with substantial potential impact on health care service needs and expenditures, and must be monitored.

With an aging population, increasing prevalence of chronic disease, and the implementation of primary care initiatives to shift some of the burden of chronic disease care from the public to the private sector, a primary care morbidity study is timely and important to document and evaluate the impact of these changes.

This study aims to determine the changes in morbidity and management patterns in Hong Kong primary care compared with the patterns identified in the morbidity study conducted in 2007-2008 [3]. Specific objectives include the following:

To identify and describe the patterns of morbidity in primary careTo determine the management patterns of primary care doctors including prescription, investigation, referral, and preventive careTo examine the differences in morbidity patterns in public and private health care sectorsTo determine the doctor and practice characteristics associated with morbidity and management patterns in primary care

## Methods

### Study Design

This is a prospective practice-based survey of Hong Kong primary care doctors that will explore the morbidity and management patterns in primary care to inform health care service and practice.

### Subjects

The target population in this study is primary care doctors in Hong Kong. We will invite doctors practicing in different primary care settings and in different regions of Hong Kong to join the study, reflecting the range of problems that may be characteristic of demographically different settings. We will include doctors working in the public (GOPCs and Department of Health clinics) and private sectors (solo practices, university health services, nonprofit organizations, and private hospital family medicine clinics).

### Sample Size Calculation

The sample size calculation is based on the first two primary objectives of our study, which are to determine the proportion of health problems/diagnoses among all clinical encounters and the proportion of various management activities in terms of prescription, investigation, referral, and preventive care. The 2007-2008 morbidity study found that respiratory conditions comprised the largest proportion of problems (36.2%) and among these, upper respiratory tract infection was the most common diagnosis (26.4%) [10]. On this basis, if we conservatively anticipate the proportion of a type of health problem/diagnosis to be 50% with a confidence interval of 95% and a maximum error of 0.5%, we will need to encounter at least 38,415 health problems over one year. This translates to about 10,000 health problems per season. In the 2007-2008 morbidity study, 109 doctors recorded 69,973 health problems over the course of the year, which meant that on average, each doctor encountered about 250 health problems in one week. Based on this estimation, 40 doctor-weeks will be required to encounter the requisite number of health problems for each season. Assuming there is a one-third dropout rate of doctors, 60 doctor-weeks per season will be required. According to a general population study on service utilization patterns in primary care, around 80% of those who visit a Western medical practitioner would attend a private clinic whereas the remaining 20% would attend publicly funded primary care services [12]. Considering this, we need 48 doctors from the private sector and 12 doctors from the public sector to participate in the study.

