### Data Collection

Data collection will take place for one week in each month of the year for 18 months starting March 2021, resulting in 18 designated weeks of data collection. This will permit evaluation of the variation in morbidity through the fifth and most serious wave of the COVID-19 pandemic in Hong Kong and across seasons, which has been a significant consideration in previous studies. Seasons may be divided into 3-month periods based on historical climatological data with spring as March-May, summer as June-August, autumn as September-November, and winter as December-February. Thus, there will be 3 weeks of data collection in each season. The study will run over 18 months to capture temporal trends as well as seasonal variation of diseases such as influenza. The first full week of each month in which there are no public holidays will be designated as the data collection week to maximize the number of working days. The week will be defined as 7 consecutive days from Sunday-Saturday as most private doctors in Hong Kong work on weekends and public GOPC are open for a half-day on Saturday. Each participating doctor will collect data on consecutive patients during any of the designated weeks of each season for a total of 6 weeks of data collected per doctor. The research team will collect all completed forms after each data collection week. All data will be checked for proper coding and be doubly entered, cleaned, and compiled into a central database for analysis.

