### Data Analysis

The patterns of morbidity in primary care will be presented by descriptive statistics for the prevalence of health problems and diseases, as well as the rates of management activities (referral, investigation, prescription, preventive care), weighted for the proportion of private and public primary care doctors in Hong Kong. The pattern of morbidity will be compared with the previous pattern in 2007-2008. All estimates will be accompanied by 95% CIs.

Stratified estimates in the patterns of morbidity in primary care by public and private doctors will also be reported and compared with the previous pattern in 2007-2008. The influence of the health care sector on morbidity patterns will be assessed by comparing the prevalence and rates of public and private doctors by nonlinear mixed effects analysis with logit link that accounts for potential covariance among health problems from the same doctor.

Factors associated with morbidity and management patterns in primary care will be assessed by nonlinear mixed effects model with logit link to cater for the dichotomous outcomes. Potential factors including patient demographics (age, sex), doctor background characteristics (age, qualifications, years of practice, type of practice, average number of consultations, participation in primary care initiatives), and nature of problem (acute, chronic, preventive) will be taken as covariates in the model. Both univariable and multivariable analyses will be performed. In the multivariable analysis, the presence of multicollinearity will be assessed by examining the tolerance. Factors involved in multicollinearity will only be considered one at a time.

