As our sample size calculation is based on the primary objective of the study, which is to determine the prevalence of health problems/diagnoses among all clinical encounters, the calculation is derived from the proportion of the most commonly occurring diagnosis encountered in the earlier morbidity study. Since the most commonly occurring diagnosis accounts for 22.7%-32.1% of encounters in any given season, the conservative estimate of 50% that we used in our sample size calculation is reasonable to calculate the total number of health problems needed to encounter per season.

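### The ±0.5% precision target is a simple-random-sample figure with no design effect, although problems are clustered within about 40–60 doctors

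*Protocol article*

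**What the plan says.** The Sample Size Calculation rests on the first two primary objectives: the proportions of health problems and of management activities. It takes a planning proportion of 50%, 95% confidence and "a maximum error of 0.5%, we will need to encounter at least 38,415 health problems over one year". It continues: "This translates to about 10,000 health problems per season". At about 250 problems per doctor-week this becomes 40 doctor-weeks per season, or 60 after a one-third dropout of doctors, and so 48 private and 12 public doctors. No allowance for clustering appears at any step.

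Data Collection has each doctor record consecutive patients in designated weeks across the seasons, "for a total of 6 weeks of data collected per doctor". Data Analysis compares the sectors with a mixed model that "accounts for potential covariance among health problems from the same doctor", and promises 95% CIs for all estimates.

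The Discussion (Overview) returns to the calculation and says that the 50% planning value "is reasonable to calculate the total number of health problems needed to encounter per season".

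**The concern.** Problems recorded by one doctor share that doctor's patients, locality, type of practice and diagnostic habits. The plan relies on such differences. It deliberately recruits from demographically different settings, and one of its objectives is to find doctor and practice characteristics associated with morbidity and management. If doctors differ, 1,000 problems from one doctor carry less information than 1,000 problems from 1,000 doctors, and precision depends mainly on the number of doctors.

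At stake is the only precision statement for the first two primary objectives. A count of problems can also suggest that the target has been reached when the precision has not. At the plan's 250 per week, the 176 doctor-weeks reported by April 2022 imply about 176 × 250 = 44,000 problems, already above 38,415. The Introduction calls a one-point change in the referral rate important, so an error of a point or more would matter to readers.

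**Working it through.** **Inputs from the document.** Proportion p = 0.50, 95% confidence, error e = 0.005, about 250 problems per doctor-week, 60 doctors recruited (48 + 12) and one-third dropout (Sample Size Calculation); 6 weeks per doctor (Data Collection).

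**Derived.** Doctors retained: 60 × 2/3 = 40. Problems per doctor: 4 seasonal weeks in a year × 250 = 1,000; 6 × 250 = 1,500.

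**Assumed.** The ICC, shown from 0.001 to 0.05. The document gives no value.

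**Step 1: reproduce the plan's figures.** n = 1.96² × p(1−p) / e² = 3.8415 × 0.25 / 0.000025 = 38,415. This matches exactly with a design effect of 1. Also 10,000 / 250 = 40 doctor-weeks, and 40 / (1 − 1/3) = 60.

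**Step 2: add clustering by doctor.** With J doctors and m problems each, the design effect is DE = 1 + (m − 1) × ICC, and the half-width is 1.96 × √[p(1−p) × DE / (J × m)].

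Worked case, J = 40, m = 1,000, ICC = 0.01: DE = 1 + 999 × 0.01 = 10.99; half-width = 1.96 × √(0.25 × 10.99 / 40,000) = 1.62 points.

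Half-width in percentage points at p = 50%:

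| Doctors × problems each | ICC 0.001 | 0.005 | 0.01 | 0.05 |
|---|---|---|---|---|
| 40 × 1,000 | 0.69 | 1.20 | 1.62 | 3.50 |
| 40 × 1,500 | 0.63 | 1.17 | 1.60 | 3.49 |
| 60 × 1,000 | 0.57 | 0.98 | 1.33 | 2.86 |
| 60 × 1,500 | 0.52 | 0.95 | 1.31 | 2.85 |

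Under a single common ICC, going from four to six weeks per doctor changes little once the ICC reaches 0.005.

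**Step 3: the largest ICC at which ±0.5 points holds.** The target requires DE ≤ J × m / 38,415.

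- 40 doctors, 4 weeks: DE ≤ 40,000 / 38,415 = 1.041, so ICC ≤ 0.041 / 999 ≈ 0.00004.
- 40 doctors, 6 weeks: DE ≤ 60,000 / 38,415 = 1.562, so ICC ≤ 0.562 / 1,499 ≈ 0.0004.
- 60 doctors, 6 weeks, no dropout: DE ≤ 90,000 / 38,415 = 2.343, so ICC ≤ 1.343 / 1,499 ≈ 0.0009.

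Since the between-doctor SD is √[ICC × p(1−p)], these limits mean that doctors' true proportions may vary with an SD of at most about 0.3, 1.0 and 1.5 percentage points respectively.

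**Step 4: less common items.** With 40 doctors × 1,000 and ICC 0.005 to 0.05, the half-width is 1.06 to 3.08 points at 26.4% (the most common diagnosis in 2007–2008) and about 0.4 to 1.1 points at 2.5% (the 2007–2008 referral rate).

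**Step 5: one season.** Under simple random sampling, 10,000 problems give 1.96 × √(0.25 / 10,000) = 0.98 points. The ±0.5 points can therefore refer only to the full year.

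**The case against.** The arithmetic is right: 38,415, 40 and 60 all reproduce. What is missing is a design assumption. The survey is descriptive, 95% CIs are promised for every estimate, and data collection is far advanced, so the achieved precision will be seen in the results whatever the planning section says. This limits the consequences, but it does not make the planning figure correct. It is printed in full for the first two primary objectives and depends on an independence that the analysis section does not assume. The article ties the within-doctor adjustment to the mixed model for the sector comparison and does not say how the descriptive CIs are formed. That detail may stand in a full analysis plan, so its absence is not counted as an error here.

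Three stronger readings are tempting and are not supported:

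- A reader might infer that the study will deliver ±1 to ±3.5 points. That range needs an ICC of about 0.005 to 0.05 and p = 50%. No ICC is given; at 0.001 the half-width is 0.52 to 0.69 points, and rarer items have smaller half-widths. Participation may also be partial. The 2007–2008 figures, 69,973 / 109, give about 642 problems per doctor. With 60 doctors and about 640 problems each, ICC 0.005 to 0.05 gives about 1.02 to 2.87 points.
- A reader might infer that the Discussion claims ±0.5 points for each season. It defends only the 50% planning value and names no margin of error.
- A reader might infer a promised precision for each sector. The calculation attaches its margin to the whole year's problems and makes no promise by sector.

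A single ICC across weeks is also a simplification. If problems from different weeks of one doctor are less correlated than those within a week, extra weeks help more than the table shows.

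**Conclusion.** The concern holds: the ±0.5% is a simple-random-sample figure that the clustered design does not support. At p = 50% it requires an ICC no larger than about 0.00004 to 0.0009, which means almost no variation between doctors in a plan built to study such variation. How far precision falls short is unknown without an ICC. Over an assumed 0.001 to 0.05, the half-width would be about 0.69 to 3.5 points with 40 doctors × 1,000 problems and about 0.52 to 2.9 points with 60 × 1,500. These figures assume equal cluster sizes and one common ICC, and leave out any extra variance from weighting by sector. The statement needs correcting because it concerns primary objectives; the number of doctors need not change.

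**What to change.** In the Sample Size Calculation, keep the planned number of doctors and replace the 0.5% maximum error with the overall half-width after a design effect of 1 + (m − 1) × ICC. Estimate the ICC from the doctor-weeks already collected, or show the half-width over a stated ICC range. In Data Analysis, state that the 95% CIs of the descriptive prevalences and management rates are computed with clustering by doctor.

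Nothing in the Discussion needs deleting. At most, add there that the ±0.5% refers to the full year and that about 10,000 problems per season give ±0.98 points even under simple random sampling.

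The cost is a recalculation and a change of text, with no further recruitment. The downside is a less favourable stated precision.

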### Recruitment of Subjects

Because there is no complete, publicly available primary care doctor register with contact information, we will undertake a targeted recruitment. We will recruit doctors in the Primary Care Research Network established during a previous study on the epidemiology of depression in primary care conducted by the Department of Family Medicine and Primary Care at The University of Hong Kong. This resulted in a network of 60 primary care doctors across 45 practices who expressed interest to participate in future research studies [14]. In addition, we will invite members of the Hong Kong College of Family Physicians, honorary teachers of the Department of Family Medicine and Primary Care at The University of Hong Kong and the Division of Family Medicine, School of Public Health at the Chinese University of Hong Kong. We will also specifically target doctors listed in the Primary Care Directory, a voluntary directory, and the doctors listed as service providers in the GOPC Public-Private Partnership Programme on the corresponding websites. Those who are interested will receive a briefing on the study by the principal investigator and/or a member of the research team and provide written informed consent if they wish to participate.

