### Data Collection Forms and Tools

#### Background Information Form

Each doctor participating in the study will provide background information including demographics, practice characteristics, training, and involvement in government-coordinated primary care initiatives. To maintain anonymity, doctors will be allocated a unique identifier to link their background information with the patient encounter data collected.

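### Targeted recruitment of Public-Private Partnership providers may raise private chronic-disease estimates, and weighting by sector alone would not correct it

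*Protocol article*

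**What the plan says.** The Abstract describes the sampling plainly: "Participants will be recruited by convenience and targeted sampling from both public and private sectors". Recruitment of Subjects explains that no complete public register with contact details exists and lists the sources. One is a research network ("This resulted in a network of 60 primary care doctors across 45 practices who expressed interest to participate in future research studies"). Others are College members and honorary teachers at two universities. Two further lists are singled out. The directory comes first: "We will also specifically target doctors listed in the Primary Care Directory, a voluntary directory". The same sentence then adds the PPP providers, described as "the doctors listed as service providers in the GOPC Public-Private Partnership Programme on the corresponding websites". No quota or expected yield is given for any source.

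The Introduction names the initiatives introduced since the 2007-2008 survey, "such as the GOPC Public-Private Partnership, Elderly Health Care Voucher Scheme, and the Vaccination Subsidy Scheme", and says that they are meant to steer patients, particularly those with chronic disease, to private care. On what the survey can show, it says: "Tracking morbidity and management trends would provide an indication of the impact of these initiatives on the prevalence of chronic disease". The sentence goes on to cover how such disease is managed in each sector.

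Data Analysis says that prevalences and management rates will be "weighted for the proportion of private and public primary care doctors in Hong Kong". Overall and sector-stratified patterns are then compared with 2007-2008. The public-private comparison uses a mixed model with a logit link, described as accounting for covariance within doctor. Participation in primary care initiatives is named only among the covariates of the separate model for associated factors. The Background Information Form collects "training, and involvement in government-coordinated primary care initiatives". Limitations discusses only COVID-19.

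**The concern.** One recruitment list is defined by participation in an initiative that is meant to change the case mix of private practice. If PPP doctors see more chronic disease than other private doctors, and make up a larger share of the private sample than of private doctors in Hong Kong, private chronic-disease prevalence is overestimated. Sector weights set how much each sector counts. They leave the mix of doctors within the private sector as recruited.

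The affected results are central. Change since 2007-2008 is the stated aim, public-private difference is a specific objective, and prevalence and its distribution by sector are primary outcomes. The likely distortion (more chronic disease in private practice, a rise since 2007-2008, a smaller gap to the public sector) is also what one would see if the initiatives had worked. A reader could not tell the two apart from the planned tables.

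**Working it through.** **1. The plan's own figures.** These set the scale. Sample Size Calculation uses a proportion of 50%, 95% confidence and a maximum error of 0.5 percentage points:

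n = z² × p(1 − p) / d² = 1.95996² × 0.25 / 0.005² = 38,414.6, rounded up to 38,415, as stated.

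Then 10,000 / 250 = 40 doctor-weeks per season, 40 / (1 − 1/3) = 60, and 60 × 0.8 = 48 private with 60 × 0.2 = 12 public. All reproduce.

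**2. Why sector weights do not help.** Let W be the private weight, and P_priv and P_pub the sector prevalences. The weighted estimate is W × P_priv + (1 − W) × P_pub. An error b in P_priv becomes W × b overall. It stays b in the private stratum, and passes in full into the public-private difference and into the private change since 2007-2008, unless offset by selection in the 2007-2008 survey.

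**3. Size of b.** With s the PPP share in the private sample, π the PPP share among private doctors, and D the difference in chronic-problem prevalence between PPP and other private doctors:

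b = (s − π) × D

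This treats doctors as recording similar numbers of problems. The document gives none of s, π or D, so the values below are assumptions. W is also an assumption: the 80% in Sample Size Calculation is the share of patients attending private clinics, whereas the analysis weights by the share of doctors, which is not given.

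| Assumed s − π | Assumed D | b, private stratum | Overall, if W = 0.8 |
|---|---|---|---|
| 10 points | 5 points | 0.10 × 0.05 = 0.5 points | 0.4 points |
| 20 points | 10 points | 0.20 × 0.10 = 2 points | 1.6 points |
| 40 points | 20 points | 0.40 × 0.20 = 8 points | 6.4 points |

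For scale, a 10-point excess with a 6.25-point difference gives 0.8 × 0.10 × 0.0625 = 0.5 points overall, equal to the planned margin. That margin is sampling precision for a single proportion, not a tolerance for bias. Recording more encounters narrows the interval but leaves b unchanged.

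**4. Cost of weighting within the private stratum.** If PPP doctors were 30% of the sample and 10% of the population (both assumed), the weights are 0.1/0.3 and 0.9/0.7. The Kish design effect is 0.3 × (0.1/0.3)² + 0.7 × (0.9/0.7)² = 0.033 + 1.157 = 1.19. Intervals widen by √1.19 − 1, about 9%.

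**The case against.** **Enrichment is not demonstrated.** The PPP list is one of several sources, the Primary Care Directory is targeted in the same sentence, and there is no quota. A reader might infer that the private doctors come from the PPP list, or that over-representation is a fact. The document supports neither. Over-representation is a likely result of targeting, no more.

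**Impact is not an objective.** A reader might also infer that the survey is designed to estimate the effect of the PPP. The Introduction promises only an indication, for several initiatives, and impact is not among the four specific objectives. This stands. The estimates at risk, however, do belong to the aim, the objectives and the primary outcomes.

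**Participation is already handled in part.** Doctor and practice characteristics are listed as confounders, and initiative participation is a covariate in the associated-factors model. An adjusted analysis is therefore planned, but it does not alter the weighted prevalences, the stratified estimates or the comparison with 2007-2008.

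**The 2007-2008 comparison.** It is tempting to say that the rise since then is biased upward. The PPP came later, so that survey had no matching enrichment, but its recruitment is not described here and may have been selective in other ways. The net bias is unknown.

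**The magnitude is assumed.** Also true: the private-stratum range runs from 0.5 to 8 points, so the effect could be trivial or large. Diagnoses with no link to the PPP may hardly be affected.

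**Detail may sit in a fuller document.** Weighting cells often do. Here, though, the article itself states the weighting variable and the targeting, and the two do not fit together.

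**Conclusion.** The concern holds in a limited form. The plan targets PPP providers, expects trends to reflect initiatives that include the PPP, and weights by sector only. Any over-representation of PPP doctors would therefore remain in the private prevalences, in their change since 2007-2008 and in the descriptive public-private contrast. The expected direction is towards higher private chronic-disease prevalence, on the assumption that PPP doctors see more of it, which is the scheme's stated purpose.

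The size cannot be derived from the document. The 2-point illustration rests on an assumed 20-point excess share and an assumed 10-point prevalence difference, and its overall counterpart of 1.6 points also rests on an assumed 80% private weight. This is a worthwhile and inexpensive improvement to the analysis, not evidence that the results are wrong.

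**What to change.** In Data Analysis:

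- Report private estimates, the 2007-2008 comparison and the public-private comparison separately for PPP and non-PPP private doctors. Use the participation item on the Background Information Form. If it does not record the PPP separately from other initiatives, match doctors to the provider list used for recruitment.
- If a count of private primary care doctors is available, also weight within the private stratum to the PPP share. The document does not state such a count. Without one, show the private and overall estimates over a range of plausible PPP shares.
- State the source of the private weight. If 80% is used, label it as an assumption.

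In Limitations, say that PPP providers were specifically targeted, and that selection through the research network, the College, the teaching posts and the voluntary directory remains uncorrected.

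The cost is one extra table and somewhat wider intervals (about 9% in the example above), with little or no new data from doctors. Changing the invitations is not recommended: collection began in March 2021, 176 doctor-weeks were in hand by April 2022, and proportional invitation would need the same denominator without controlling who volunteers.
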